### Encouraging Adherence

To support participants’ adherence to the interventions, study staff reviewed relevant expectations in detail for participants at each laboratory visit. A reminder card with the week’s instructions and next laboratory appointment was provided as well as a troubleshooting guide for operation of the CReSS Pocket device. Incentive payments were provided for returning cigarette butts as well as for correct usage of the CReSS device.

### Outcome Measurements

#### Knowledge and Attitudes Toward Unfiltered Cigarettes

Participants were asked at enrollment and at the final visit to what extent they believed that the filter on their brand of cigarettes (1) protects them from health problems caused by smoking and (2) makes smoking more pleasurable. Response options included the following: not at all, a little, quite a bit, and a great deal. In addition, they were asked “If filtered cigarettes were no longer available, what, if anything, would you change about your smoking patterns?” Response options included the following: increase number of cigarettes I smoke, nothing, cut back, and try to quit smoking altogether [22]. Participants were also asked about the purpose of filters on cigarettes, with the following response options (more than one answer was accepted): making cigarettes safer to smoke, making it easier to begin smoking, making it more pleasurable to smoke, selling more cigarettes, making cigarettes cheaper, and other. Finally, participants were asked what filters are made of, with the following response options (more than one answer was accepted): cotton, food starch, asbestos, plastic or cellulose acetate, and other [23,24].

Questions at enrollment and the final visit also covered the following: possible environmental consequences of smoking (eg, whether discarded butts are a problem for the environment and what should be done to prevent these consequences), if they had previously smoked unfiltered cigarettes, and what they would do if filtered cigarettes were no longer available for purchase.

At each lab visit, participants smoked a cigarette and answered questions from the Cigarette Evaluation Scale [25]. These questions included the following: Was it satisfying? Did it taste good? Did it make you dizzy? Did it calm you down? Did it help you concentrate? Did it make you feel more awake? Did it reduce your hunger for food? Did it make you feel nauseous? Did it make you feel less irritable? Did you enjoy the sensations of the smoke in your throat and chest? and Did it immediately reduce your craving for cigarettes? Each item was rated on a numbered 7-point Likert scale, ranging from 1 (not at all) to 7 (extremely). Subscales included Smoking Satisfaction, Psychological Reward, Aversion, Enjoyment of Respiratory Tract Sensations, and Craving Reduction. Response order was the same for all scales.

#### Intention to Quit

Participants were asked at each visit “What best describes your intentions to stop smoking completely, not even a puff?” Response options included the following: never expect to quit, may quit in the future but not in the next six months, will quit in the next six months, and will quit in the next 30 days [13]. In addition, they were asked whether they have currently set a limit for how many cigarettes they smoke per day to decrease health risks from smoking [26].

#### Nicotine Dependence

The Fagerström Test for Nicotine Dependence [27] was administered at enrollment and at the final visit, and a single-item index of addiction to cigarettes (0-100) [28] was established at every visit. The Brief Wisconsin Inventory of Smoking Dependence Motives was also assessed at enrollment (ie, baseline) and at the final visit [29].

#### Cigarettes Per Day: Self-Report and Butt Count

Standard survey questions measured how many days in the past month (enrollment [ie, baseline] visit), past week (weekly visits), and past 2 months (final visit) participants have smoked, as well as how many CPD they have smoked on those days (all study visits). In addition, participants returned their cigarette butts in a sandwich-size Ziploc bag or glass jar each week to provide a validation of their self-report. While these butts were disposed of as toxic waste in approved containers, a small portion were retained for future analyses. Previous studies have included butt counts with reliability set at 75% of returns [30]. We excluded butt count data from participants who did not return 75% of butts and provided incentive payments for returning cigarette butts at this level.

#### Smoking Topography

Behavioral adaptations were measured by ST, including puff number per cigarette, average puff duration (seconds), average interpuff interval (seconds), average flow rate (mL/s), and average and total volume (mL) [14]. We used the portable CReSS device to measure topography over five, daily, 8-hour periods per week: at baseline (Week 1), during the initial switch (Weeks 2 and 3), at postwashout baseline (Week 7), and again after the crossover switch (Weeks 8 and 9). Participants were trained in the use of the device by the study team at the initial lab visit in a specialized facility designed with proper ventilation to accommodate indoor smoking research. Multiple days of measurement allowed for assessment of reliability and sensitivity of topography changes as a function of the filtered and unfiltered cigarette switch. Topographic measures by CReSS have been compared to direct observation via video recordings [15]. One limitation of the CReSS device is inconsistent methodology and guidelines in calibration settings and standard usage, as well as established acceptable ranges of ST variables (eg, peak flow rates, interpuff interval, etc). However, past studies have mainly used manufacturer guidelines with added modifications and/or adaptations [31], and these were recommended in a recent review [32]; there are no changes in recommendations for newer devices.

#### Expired Carbon Monoxide

Expired CO provides a measure of exposure to tobacco smoke and other air pollutants. An expired CO breath test was conducted at each visit with the coVita Micro+ Smokerlyzer device (Bedfont) to assess expired CO levels.

#### Cotinine

Cotinine is the main proximate metabolite of nicotine. Urinary cotinine was measured at each visit by liquid chromatography–mass spectrometry (LCMS) [33] and normalized for urinary creatinine. The correlation between urinary and plasma cotinine is improved by adjusting the urinary cotinine levels for urinary creatinine concentration, which takes into account the variations in urinary dilution between samples [34].

#### Tobacco-Specific Nitrosamines

Tobacco-specific nitrosamines are carcinogens found in tobacco and tobacco smoke. Excretion of the carcinogen biomarker NNAL, which will be normalized for urinary creatinine, will be measured by LCMS [23] in urine samples. In addition, carcinogenic VOCs, excreted as mercapturic acids, will be measured from urine samples. Both are useful biomarkers of changes in exposure to tobacco smoke [35,36]. These metabolites, along with expired CO, provide biomarkers of exposure, thus creating a battery that reflects risks for smoking-induced diseases [37] that may vary between filtered and unfiltered cigarette smoking.

### Safety Monitoring Questions

Respiratory effects were assessed at every visit by asking participants about shortness-of-breath episodes or awakening from sleep due to breathing difficulties during the past 2 weeks (yes/no). Nicotine toxicity was assessed at every visit by asking whether the following symptoms were experienced in the last 2 weeks: nausea and/or vomiting, nervous irritability beyond normal day-to-day stresses, tremors, rapid heart rate, nightmares, and chest pains (yes/no). Blood pressure was also monitored at every visit.

### Criteria for Discontinuing or Modifying Allocated Interventions

Serious adverse events will result in discontinuation of the intervention; these are defined as any of the following:

Events that have resulted in death.Events that are life threatening.Events that require inpatient hospitalization.Events that result in persistent or significant disability or incapacity.Any other adverse event that, based upon appropriate medical judgment, may jeopardize the subject’s health and may require medical or surgical intervention to prevent one of the other outcomes listed in this definition.

Study personnel will notify the principal investigator (PI) of any serious adverse events immediately after first awareness of the problem. The PI will immediately report serious adverse events to the Institutional Review Board (IRB) and the Data Safety and Monitoring Board (DSMB).

### Participant Timeline

There will be a 1-week baseline period; a 2-week period of smoking filtered or unfiltered cigarettes, which will be determined at the time of randomization; and a 3-week washout period. This will be followed by a postwashout baseline week and a crossover to 2 weeks of smoking the opposite condition (see Figure 1).

**Figure 1 figure1:**
[figure not shown]
Study design diagram of the randomized crossover clinical trial of unfiltered cigarettes. CO: carbon monoxide; CReSS: Clinical Research Support System.

### Sample Size

The study sample size is 40 participants, sufficient to detect moderate within-subject effect sizes (*f*=0.35) with a moderate correlation between repeated measures (*r*>0.50). This two-by-two crossover design has statistical power of 80% for a sample size of 20 in each group to detect an effect size of 10% change in average number of cigarettes smoked per day. We tried to recruit at least 10 participants of non-White ethnicities. If participants prematurely discontinued from the trial prior to crossover, we attempted to recruit replacements from the eligible pool or advertise for new participants. We recruited 20 women out of the 40 participants and randomized by sex. Sex stratification is of interest because men and women may metabolize smoke differently due to differences in body size and differences in cigarette preference and behavior. Any woman who becomes pregnant during the trial will be excluded from further participation [38].

### Recruitment

Recruitment was accomplished using a combination of Craigslist postings, newspaper ads, and paper flyers, which are approaches that have been successfully used in previous studies by the study team [39,40]. Prospective participants responded to advertisements via telephone or email to learn more about the study and to coordinate a time for phone screening to determine eligibility. Former participants in studies conducted at Institution B who have expressed interest in being contacted for future studies were contacted and invited to complete the screening questionnaire.

### Assignment of Interventions: Allocation

Once a participant was deemed eligible for the trial remotely by Institution A, trial personnel at Institution B followed up with the participant to schedule the initial trial appointment (ie, the enrollment, or baseline, visit). Participants who did not meet the eligibility criteria were not included in the trial. Recruitment and enrollment was a continuous process (ie, up to 10 participants at a time), which enabled us to utilize topography devices and lab facilities most efficiently. Randomization, stratified by sex, was based on a table of random numbers, and records were placed in sealed envelopes. A total of 20 participants were assigned to be first switchers following their enrollment (ie, baseline) visit at Institution B. These participants were then tested on individualized schedules (ie, not as a group), with each participant committing to 9 weeks of trial time, including a washout period at midtrial. All subjects had first smoked filtered Camel or Pall Mall cigarettes for at least two weeks prior to beginning the trial, according to the inclusion criteria. This standardized their exposure to a brand that was used as an unfiltered variety in the trial.

### Assignment of Interventions: Blinding

Investigators were masked to group allocation, but participants and research staff knew their exposure assignment due to the difficulties of blinding cigarettes that were filtered versus not filtered. DSMB members were unblinded to group allocation if needed.

### Plans for Assessment and Collection of Outcomes

There were eight scheduled lab visits, each with an incentive for attendance (see Participant Retention and Complete Follow-Up section). As shown in Table S1 in Multimedia Appendix 2, these visits were to occur weekly at baseline (Week 1), during the first 2 weeks of cigarette use (Weeks 2 and 3), during the postwashout baseline (Week 7), and during the second 2 weeks of cigarette use (Weeks 8 and 9). During each visit, participants were tested for expired CO, had blood pressure and weight measurements performed, and completed surveys (see Table S1 in Multimedia Appendix 2). At Weeks 1, 3, 7, and 9, participants provided a urine sample to measure normalized cotinine and carcinogen biomarkers. All collected urine samples were stored in a –80 °C freezer. Specimens were transported from Institution B to Institution A for laboratory testing.

During visits 2-4 and 6-8, participants visited the Institution B smoking laboratory facility with their topography device, cigarette butts, and unused cigarettes (left only on Weeks 3, 4, 7, and 8). Data from the topography device were downloaded so that the number of cigarettes logged in as smoked on the CReSS device could be compared to the total number of cigarettes or butts returned, as well as the number self-reported cigarettes smoked per day. Those deemed compliant with study procedures were paid for their time and supplied with another weeks’ supply of condition-assigned cigarettes. During visit 8, the same procedure was to be followed, except that it would be the final visit and no additional study cigarettes would be provided. Due to the COVID-19 pandemic, some of these procedures were curtailed and moved to remote follow-up.

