### Eligibility Criteria

#### Inclusion Criteria

Participants met all of the following criteria: aged 21-65 years; smokers of 5 or more cigarettes per day (CPD) on 25 or more days per month for 1 year or more; smokers of Camel or Pall Mall filtered cigarettes for at least two weeks prior to enrollment, and willing to continue using this brand during the study; fluent in English; have regular telephone access; and have transportation to attend all scheduled visits. Participants must have primarily (ie, ≥50% of the time) smoked cigarettes, allowing for secondary use of other tobacco products. We verified their regular smoking status upon enrollment with an expired CO level of at least 10 ppm [19]. Because we expected to be able to detect changes in our primary outcomes at lighter levels of smoking [20,21], we included light smokers in the study.

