### Study Cigarettes

Two brands of cigarettes are currently available as filtered and unfiltered: Camel and Pall Mall. Participants were provided supplies of one of these two brands throughout the study period based on their preference. After baseline measurements at the beginning of Week 2, we randomly assigned participants to smoke 2 weeks’ worth of filtered or 2 weeks’ worth of unfiltered study cigarettes. We supplied study cigarettes according to the average cigarettes smoked per day for the previous week plus 10%. For example, a participant who reported smoking 10 CPD in the previous week would be provided with a supply of cigarettes that would allow 11 CPD for the entire 2-week trial. Although it is possible that changes in CPD might result from increased supplies, participants were encouraged to smoke as normally as possible and to return any unused study cigarettes in order for us to measure changes in CPD resulting from switching.

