### Statistical Methods

#### Primary and Secondary Outcomes

Descriptive statistics will be used to analyze baseline data to assess any imbalances between groups in baseline demographics and prerandomization characteristics. Stratified analyses and analyses of covariance will be performed to control for any baseline imbalances. To account for the crossover design and repeated measures, linear mixed-effects models with fixed effects for period and exposure sequence (ie, filtered then unfiltered or unfiltered then filtered) and with random effects for sex and participant will be used to analyze continuous outcomes and changes from baseline. Log transformation of nonnormal continuous measures will be performed when necessary. If data do not fit a linear model, generalized models will be considered. Model variance will be fit using a compound symmetry correlation structure with default degrees of freedom, which assumes constant variance between periods, with alternative covariance structures explored in the event of nonconvergence. For analysis of ordinal questionnaire data, we will assess for exposure and period effects using ordinal repeated-measures models with fixed effects for exposure sequence and period and with random effects for sex and participant. Prespecified cutoffs and thresholds for biomarkers and topography variables will be chosen based on a comprehensive literature review prior to conducting any analysis. Normalization and sensitivity analysis will be performed, if required. Changes in means for each continuous measure between participants and between weeks within treatment conditions will be calculated. Mean differences between exposure arms for these continuous measures will also be compared. *P* values and 95% confidence intervals will be reported when providing results from fitted models. All analyses will be performed using SAS 9.4 (SAS Institute) [41]. Noncomplier and dropout data will be utilized in mixed methods models up to the point of dropout and noncompliance for an intent-to-treat analysis. A completer-only (ie, per-protocol) analysis will also be run as a secondary analysis.

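### The second week of assigned cigarettes depends on an undefined compliance judgment made after randomization, and data are then cut at noncompliance in an analysis labelled intent-to-treat

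*Protocol article*

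**What the plan says.** Plans for Assessment and Collection of Outcomes describes the visits at which participants bring back the topography device, butts and unused cigarettes. The device log "could be compared to the total number of cigarettes or butts returned, as well as the number self-reported cigarettes smoked per day". The text then continues: "Those deemed compliant with study procedures were paid for their time and supplied with another weeks’ supply of condition-assigned cigarettes". It gives no criterion for compliance and does not say what a participant judged noncompliant received.

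The same section places the urine samples: "At Weeks 1, 3, 7, and 9, participants provided a urine sample to measure normalized cotinine and carcinogen biomarkers".

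Study Cigarettes describes supply without any compliance condition: "we randomly assigned participants to smoke 2 weeks’ worth of filtered or 2 weeks’ worth of unfiltered study cigarettes". In its example, a participant reporting 10 cigarettes per day (CPD) "would be provided with a supply of cigarettes that would allow 11 CPD for the entire 2-week trial".

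The Blinding section says that investigators were masked, but that research staff and participants knew the assignment.

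Primary and Secondary Outcomes, under Statistical Methods, says: "Noncomplier and dropout data will be utilized in mixed methods models up to the point of dropout and noncompliance for an intent-to-treat analysis". It adds: "A completer-only (ie, per-protocol) analysis will also be run as a secondary analysis".

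**The concern.** The stated aims compare 2 weeks of unfiltered with 2 weeks of filtered smoking. If the second week of product depends on how the participant performed in the first, the exposure itself is conditional on behaviour after randomization. If data are also dropped from that point, the second-week comparison no longer covers everyone assigned.

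Compliance in the unfiltered condition may depend on how the participant reacted to unfiltered cigarettes. That reaction is close to what the trial measures, through satisfaction, topography, consumption and exposure. Selection on it can push the contrast in either direction, and the intent-to-treat label would hide that it happened.

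**Working it through.** **Step 1: the supply rule.** Study Cigarettes sets a quantity (previous week's CPD plus 10%) for two weeks, unconditionally. The visit section has a further week's supply handed out to those judged compliant. If both weeks were issued at once, the resupply sentence has no function. If supply was weekly and conditional, the 2-week description does not hold for everyone. The text does not say which happened.

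**Step 2: what the judgment covers.** The only check described at that visit compares device log, returned cigarettes or butts, and self-report. These are mainly measurement behaviours. No threshold is attached to supply.

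**Step 3: what falls in the second week.** Weeks 3 and 9 are the second weeks of the two conditions. The Overview agrees, placing urine collection before washout and at the end of the study. NNAL and VOC therefore have one sample per condition, in the week that depends on resupply. Cotinine is less clear, because the Cotinine section says it was measured at every visit. CPD, expired CO and topography are also recorded in Weeks 2 and 8.

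**Step 4: data cut at noncompliance, as the Statistical Methods state.** Let q be the share cut, δc the true second-week effect in compliers, and δn the effect noncompliers would have shown if supplied. The target is (1 − q)δc + qδn, and the retained data estimate δc. So bias = q(δc − δn), and its sign is unknown. As an illustration, if δc and δn differed by 10 percentage points (the size of the CPD effect used for power), the bias would be 0.5, 1, 2 or 3 points at q = 5, 10, 20 or 30%. A participant cut in period 1 may also lose period 2, and with it the within-person contrast.

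**Step 5: later data kept.** Participants' own product is filtered ("smokers of Camel or Pall Mall filtered cigarettes for at least two weeks prior to enrollment"). If unsupplied participants went back to it, exposure would change only in the unfiltered condition, and the second-week contrast would shrink by the factor 1 − q.

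**Step 6: the effect on power, as illustration.** The stated 80% power for a 10% change in CPD with 20 per group cannot be reproduced, because neither a standard deviation nor alpha is given. Readings of f = 0.35 with r = 0.5 at N = 40 give 0.58 to 0.99, depending on convention. Back-solving instead (2×2 crossover, two-sided 0.05 assumed, noncentral t, N − 2 df), 80% at N = 40 needs a standardized within-person difference dz = 0.455. That is a standard deviation of the difference of 10/0.455 ≈ 22% of mean CPD. At the 37 enrolled, power is 0.77 before any noncompliance.

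- Data kept: dz becomes (1 − q)(0.455)/√(1 + q(1 − q)(0.455²)), with N = 40. Here q is the share unsupplied in the unfiltered condition.
- Data cut wholly at random: dz stays at 0.455 and N = 40(1 − q). Here q is the share lost from the second-week pair.

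| q (assumed) | Kept: true 10% effect becomes | Kept: power | Cut: N | Cut: power |
|---|---|---|---|---|
| 5% | 9.5% | 0.754 | 38 | 0.778 |
| 10% | 9.0% | 0.705 | 36 | 0.755 |
| 20% | 8.0% | 0.597 | 32 | 0.701 |
| 30% | 7.0% | 0.484 | 28 | 0.639 |

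These rows concern a second-week contrast only. If both weeks count equally, as they may for CPD, the attenuation with data kept is 1 − q/2. By the normal approximation Φ(2.802(1 − q/2) − 1.960), power is then about 0.76, 0.71 and 0.66 at q = 10, 20 and 30%.

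**The case against.** The strongest defence is that this is one condensed sentence. Study Cigarettes may fix the quantity while the visit section describes weekly handing-out, and the two can coexist. Compliance might mean smoking the assigned product. Payment is itemised elsewhere (10 dollars per device-day, 30 for butts, 20 for attendance), which does not fit an all-or-nothing test. The appendix on participant activities is not shown, and perhaps nobody was refused supply. These points stand as reasons not to assume the worst. They do not remove the problem, because the article states a condition on the exposure itself, which is more than omitted detail, and elsewhere describes supply without it.

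A reader might go further and infer that noncompliers returned to filtered cigarettes, so that only the unfiltered condition was diluted and every outcome biased toward no difference, with power near 50% at q = 30%. The documents do not support this:

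- No section says what unsupplied participants smoked. They might have been supplied anyway, retrained, or discontinued and replaced, and unfiltered versions are on general sale.
- The stated analysis stops at noncompliance, so later data would not enter under the unfiltered label.
- CPD, CO and topography also have first-week data in each condition.
- The range for q has no source in the article.

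**Conclusion.** The point holds as a conflict between three sections with a consequence for the analysis. As written, the second-week comparison can rest on a subset chosen after randomization by an undefined criterion, applied by staff who know the assignment, and the label intent-to-treat does not describe it. NNAL and VOC are most exposed, since they have no first-week sample to fall back on. The direction of bias is unknown. Its size is q times the difference in response between compliers and noncompliers, and neither is given. One-sided dilution is a conditional second route that needs two further assumptions. The power figures illustrate assumed rates and are not estimates for this trial. If no participant was refused supply or cut for noncompliance, the effect is nil, and reporting those counts would settle the matter.

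**What to change.** Conduct is reported complete and analysis is underway, so the changes fall on reporting and analysis.

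1. Reconcile Study Cigarettes, Plans for Assessment and Collection of Outcomes, and Statistical Methods. State whether supply depended on measurement compliance, how compliance was judged, and what noncompliers received. Discontinuation for serious adverse events is not affected.
2. Flag for each participant-week whether assigned cigarettes were supplied, including Weeks 2 and 8 to confirm first-week supply. Report by condition the numbers unsupplied and the numbers cut for noncompliance.
3. For the analysis labelled intent-to-treat, use all collected measurements by assigned condition. Give the analysis that stops at noncompliance a different name. Keeping later data opens the dilution route, so the supply counts should stand beside the result.
4. Add a Week 2 against Week 8 contrast for CPD, CO and topography, before resupply within the condition comes into play, beside the Week 3 against Week 9 contrast.

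The cost is one flag per participant-week, a short table and one extra contrast, that is, a little more analysis and reporting work. No new data collection is needed if supply records can be recovered. A larger follow-up trial would need the reconciled wording before it adopts this procedure.
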